#### Adult patients lacking mental capacity

On hospital admission, the patient’s capacity will be assessed in accordance with the Mental Health Capacity Act (2005). Given the nature of this study, patients, either on, or shortly after their arrival at the emergency department, may lack capacity due to the severity of their injuries or as a consequence of sedation and/or ventilation. A patient may also lack capacity due to a pre-existing comorbidity. If a patient does not have the capacity to make an informed decision, the burns research team will approach a patient’s personal consultee (eg, next of kin, relative, carer or friend). In instances where a personal consultee is not available, a nominated consultee will be sought. Nominated consultees are considered to be medical professionals that have no connection to the research study, but have an understanding of its implications on the participant. Examples of nominated consultees who will be approached include: emergency department doctors, intensive care doctors or doctors from the burns team that are not directly involved in the SIFTI-2 study. The rationale for the use of nominated consultees is that the physiological response to burn trauma is ongoing from the time of injury. As such, while efforts are being made to contact their next of kin, this system of consent enables research blood samples to be obtained during the early postinjury phase that would otherwise be missed.

Once a personal or nominated consultee has been identified, they will be provided with a study specific information leaflet. If in their opinion, the patient would have no objection to being recruited into a research study, the consultee will be asked to sign a declaration form. When the patient regains capacity, the study will be explained to them and they will be asked for their consent for the data obtained so far to be used and for any future sampling. If the participant declines consent, the data collected will be deleted and no further sampling undertaken. In instances where the patient does not regain capacity, their data will be included into the study in accordance with the legal consultee’s assent.

#### Children (aged <16 years)

A child will be recruited into the SIFTI-2 study in one of three ways:

##### Parental/legal guardian consent

All children will be consented into the SIFTI-2 study by their parent or legal guardian. If, after an explanation of the study, the parents/guardians have no objection to their child’s involvement in the study, they will be asked to sign the parental consent form on behalf of the child.

##### Child consent

As all children will be consented into the study by their parent or legal guardian, no child can self-consent for study enrolment. However, children deemed psychologically and emotionally mature, and who meet the Gillick Competence criteria,^21^ will be able to consent to their study involvement. The child will be provided with information on the study and, if after a discussion with the burns research team, agree to participate, they will be asked to sign the child consent form. This is to ensure that children of a certain level of maturity understand what is being proposed and that they agree with joining the study. Thus, the child’s consent is a matter of confirming their agreement with the adult consent. If any child, who was deemed Gillick competent, does not wish to give their consent, then they would not be recruited into the study, even if the legally responsible adult had consented. If the child is not consenting, they do not join the study.

##### Deferred consent

A model of deferred consent will be used in situations where the clinical or research team feel initial parental/guardian consent is not appropriate and may cause further undue stress. Under this model, children will be enrolled by the burns or critical care team on admission so that day 1 and day 2 blood samples can be obtained. Parents/guardians will then be approached about the study and provided with an information sheet within 48 hours of their child’s hospital admission. Parental/guardian consent should be obtained within this 48-hour period. If consent for future study involvement is refused, then consent to keep the initial clinical and laboratory data will be sought. If refused, then all data will be destroyed.

#### Withdrawal of consent

Participants may withdraw or be withdrawn from the study at any time, the reason for which will be collected and recorded in the electronic case report form (CRF). Any data or samples collected at the time of withdrawal may still be included in the data analysis, unless a participant specifically withdraws consent. Participants will be asked to clarify this at the point of withdrawal.

It is possible that a participant maybe withdrawn from the study by the Sponsor, for non-compliance with study procedure. Such criteria for this include: (1) subject withdrawal of consent, (2) subject non-compliance, (3) any medical condition not compatible with continuation of the study and (4) as a result of safety review and recommendation.

### Sample size

The sample size for this study is based on data collected from adult patients recruited into the SIFTI-1 study.^18^ Of the 57 adult burns patients who survived for at least 7 days following study enrolment, 35 developed sepsis, equating to a prevalence of 61%. Of these, 33 patients, with a TBSA burn ≥15%, had measurements of neutrophil phagocytic capacity, plasma cfDNA levels and IG count recorded on day 1 of injury. These data provided good discriminatory power to identify septic patients, with logistic regression modelling providing an area under the ROC of 0.935. Adjusted for shrinkage following internal bootstrap model validation to account for potential overfitting, this model exhibited a specificity of 0.75 and a sensitivity of 1.00. Based on this information, we computed the sample sizes required to estimate a 95% CI for sensitivity (with a maximum width of 10%) and for specificity (with a maximum width of 20%) for prevalence rates of sepsis ranging from 50% to 70%. Assuming a prevalence of sepsis of at least 60% and that the ‘true’ sensitivity is at least 90% and the ‘true’ specificity is at least 70%, these analyses revealed a total of 220 patients would allow us to reliably rule out a sensitivity less than 84% and a specificity of less than 59%. Assuming that the 10% drop-out rate we recorded for patients over the first 7 days of the SIFTI-1 study holds true for this follow-on study, then a total sample size of 245 burns patients, which includes both adult and paediatric age groups, is required for the SIFTI-2 study.

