## Introduction

Built on such clinical practices as early burn excision and wound closure, goal-directed fluid resuscitation and early enteral feeding, modern day burn care has markedly improved the initial outcomes of thermally injured patients, who now survive injuries that were fatal less than 30 years ago.^1^ However, with such unprecedented survival rates, new challenges in the management of hospitalised burns patients have emerged. With an incidence rate of between 23%–63% in paediatric burns patients^2–4^ and 8%–42.5% in adult burns patients,^5^ sepsis is a common complication following thermal injury. Defined as ‘life-threatening organ dysfunction caused by a dysregulated host response to infection’,^6^ postburn sepsis is associated with significantly increased lengths of intensive care unit and hospital stay, and is the leading cause of mortality among hospitalised burns patients, accounting for between 28%–65% of deaths in adult patients^5^ and 47% of deaths in paediatric patients.^7^ Understanding the mechanisms underlying the development and progression of sepsis is therefore critical if we are to improve patient outcomes postburn.

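### The stated precision (lower limits of 84% for sensitivity and 59% for specificity with 220 patients) holds only near 60% sepsis prevalence, not at 60% or more, and is worded too firmly

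*Protocol article*

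**What the plan says.** The Sample size section (Protocol article) reports sample sizes worked out against two precision targets. One is "to estimate a 95% CI for sensitivity (with a maximum width of 10"%; the other allows the specificity interval up to 20 points. The planning grid covered sepsis prevalences between 50% and 70%. The section then fixes the planning case: "Assuming a prevalence of sepsis of at least 60"%, with a true sensitivity of 90% or more and a true specificity of 70% or more. From this it concludes that 220 patients reliably exclude a sensitivity below 84% and a specificity below 59%. Allowing for 10% drop-out gives 245 patients, adults and children together.

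The same section gives the source of the prevalence: 35 of 57 adults in the earlier study who survived at least 7 days, or 61%. The Introduction describes sepsis rates more broadly. For adults it cites "8%–42.5% in adult burns patients"; for children the range given is 23% to 63%.

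**The concern.** Sensitivity is estimated in septic patients only and specificity in non-septic patients only. At a fixed total of 220, a change in prevalence makes one estimate more precise and the other less so. A condition of the form "60% or more" therefore cannot protect both bounds: below 60% the sensitivity bound slips, and above it the specificity bound does.

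The floor is also firmer than its source. It comes from one adult sample restricted to 7-day survivors, but the new cohort includes children and several centres. The Introduction cites rates that are mostly lower than 60%.

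Readers will use this paragraph to judge how tightly the validation can pin down sensitivity, the quantity given the narrower target width. If the paragraph promises more than the design gives, a final interval that dips below 84% could be taken as a failure of the biomarkers when it was always a likely result.

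**Working it through.** **Inputs (Sample size section).** Evaluable N = 220; sensitivity 0.90; specificity 0.70; prevalence 60%, within a grid of 50% to 70%; target widths 10 and 20 points; drop-out 10%; pilot 35/57. Width is taken as upper minus lower limit.

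**Reproducing the plan's figures.** Septic n = 220 × 0.60 = 132; non-septic n = 220 − 132 = 88. The exact (Clopper-Pearson) lower limit for x events in n is the 2.5% quantile of Beta(x, n − x + 1), and the upper limit is the 97.5% quantile of Beta(x + 1, n − x). Expected counts are used and may be fractional.
- Sensitivity, x = 118.8, n = 132: lower limit 83.6%, which rounds to 84%.
- Specificity, x = 61.6, n = 88: lower limit 59.3%, which rounds to 59%.
- Wald limits would give 85% and 60%, and Wilson limits 84% and 60%. Of the three, only the exact method matches both printed bounds.
- Enrolment: 220/0.9 = 244.4, so 245.

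All four printed figures (220, 84%, 59%, 245) are reproduced.

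**The same calculation at other prevalences** (220 evaluable, observed sensitivity 90%, observed specificity 70%):

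| Prevalence | Septic / non-septic | Sensitivity: lower limit (width) | Specificity: lower limit (width) |
|---|---|---|---|
| 40% | 88 / 132 | 81.8% (13.6) | 61.4% (16.2) |
| 42.5% | 94 / 126 | 82.1% (13.2) | 61.2% (16.6) |
| 50% | 110 / 110 | 82.8% (12.1) | 60.5% (17.8) |
| 60% | 132 / 88 | 83.6% (11.0) | 59.3% (20.0) |
| 65% | 143 / 77 | 83.9% (10.5) | 58.5% (21.4) |
| 70% | 154 / 66 | 84.1% (10.1) | 57.5% (23.2) |

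The sensitivity limit rounds to 84% from 130 septic patients upwards (130/220 = 59.1%). The specificity limit rounds to 59% from 78 non-septic patients upwards, that is, at most 142 septic (142/220 = 64.5%). Both printed bounds therefore hold together only between about 59% and 65%. At 65% the specificity bound is missed only narrowly (58.49%).

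**Width target.** At 60% prevalence the exact sensitivity interval is 11.0 points wide. A width of 10 points needs 158 septic patients, so 158/0.60 = 263.3, or 264 evaluable. The Wald formula also needs more than 220: 139 septic, so 139/0.60 = 231.7, or 232 evaluable. Specificity meets its 20-point target at 60% but not at 65% or 70%.

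**Chance of reaching the sensitivity bound.** With 132 septic patients, the exact lower limit is at least 83.5% when 119 or more test positive. P(X ≥ 119) for X ~ Binomial(132, p) is 55% at p = 0.90, 83% at p = 0.92 and 99% at p = 0.95. With 94 septic patients (42.5% prevalence) the corresponding chances are about 40%, 66% and 95%.

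**Support for 60%.** 35/57 = 61.4%, exact 95% CI 47.6% to 74.0%. The interval extends well to both sides of 60%.

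**The case against.** The strongest reply is that nothing is miscalculated. The printed figures reproduce, and the sentence states its conditions openly. A reader might infer an arithmetic error, or a claim that sensitivity below 84% is excluded whatever the prevalence. The document supports neither reading: it ties the bounds to an assumed prevalence and to assumed true values, and it does not say that 84% holds at 50%.

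A reader might also infer from the Introduction that 60% is simply wrong and that the bound fails at most realistic rates. That does not follow. The cited ranges carry no stated burn-size limit, whereas this study enrols only burns of at least 15% TBSA in adults and 20% in children. It also keeps the earlier study's sepsis definition and primary recruiting site. For this cohort the pilot rate is the closer guide. The cited rates justify a robustness check, but they do not refute 60%, and the bottom of the adult range is not a credible planning scenario here.

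Three further points are fair. The loss in the sensitivity limit is small in the plausible range: 0.8 points at 50% and 1.5 points at 42.5%. The chance of reaching the bound is high if true sensitivity is well above 90%, and the pilot estimate was 1.00. A table for the 50% to 70% grid may exist in the full protocol, so its absence from the article is not a fault.

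This leaves three faults in the text as printed. The one-sided condition is untrue for specificity towards the top of the plan's own grid. The 10-point width is not met at the planning case. Reliable exclusion is not what a 55% chance at the stated minimum sensitivity provides.

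**Conclusion.** The concern holds as a point about an unprotected planning assumption and over-firm wording. The precision statement is right at about 60% prevalence, but not across all prevalences of 60% or more. Across the plan's own grid the sensitivity limit runs from 82.8% to 84.1% and the specificity limit from 60.5% down to 57.5%. At 60% the sensitivity interval is 11.0 points wide, not 10, and the chance that its lower limit rounds to 84% or more is about 55% at true sensitivity 90%.

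The shifts are modest and do not call for a different sample size. The figures assume 220 evaluable patients, exact limits (the method that reproduces the printed bounds), and observed values equal to the planned 90% and 70% for the limits and widths. The true prevalence in this mixed cohort is not known from the document.

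**What to change.** Keep N = 245 and revise the Sample size paragraph:

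- Replace the floor of 60% with about 60% (pilot 35/57, 95% CI 48% to 74%).
- Give the expected lower limits and widths for sensitivity and specificity by prevalence, over the 50% to 70% grid and extended down to about 40%. The table above can serve.
- Replace the wording of reliable exclusion with expected lower 95% limit.
- Correct the sensitivity width to about 11 points at 60% prevalence.
- State that the precision of sensitivity depends on the number of septic patients accrued.

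This costs one reworded paragraph and a small table, with no extra patients. The downside is that the stated precision becomes slightly less favourable.

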We will determine in how many participants the measurements of neutrophil phagocytic capacity, plasma cfDNA levels and IG count on day 1 of injury predicted a diagnosis of sepsis. This proportion will be reported along with 95% CIs calculated by binomial exact methods. The accuracy of this day 1 biomarker model will be determined through standard estimates of sensitivity, specificity, predictive values and likelihood ratios, with 95% CIs. We will investigate the value added by this day 1 biomarker test when compared with information obtained from other potentially informative sets of biomarkers (eg, revised Baux score). These combinations of tests will be assessed using logistic regression models. Using multivariable logistic regression analysis, we will also generate predictive probabilities for various combinations of these candidate biomarkers. This logistic modelling will aim to derive a prognostic regression function (ie, probability of sepsis) using the day 1 values of each candidate biomarker and other demographic or burn-related variables. Models of varying complexity may be compared through ROC analyses. Longitudinal data collection will enable us to examine how the performance of these models change over time. Limitations associated with the logistic regression approach lie mainly in its generalisability to other data sets. Thus, techniques such as bootstrapping to enhance generalisability will be applied for model validation. In sensitivity analyses, missing data will be estimated by multiple imputation and maximum-likelihood methods, as appropriate, in order to explore the potential bias and reduced statistical power associated with listwise deletion.

Serial sampling will allow for repeated measures analyses of our candidate biomarkers, enabling us to model their kinetics over time and examine how this differs between septic and non-septic patients. For the analysis of longitudinal data, continuous outcomes will be analysed using linear regression to compare the septic and non-septic groups, with mean differences and 95% CIs reported. For other outcomes, analysis of daily measurements will be performed using generalised linear mixed models to account for the hierarchical structure of the data. Summaries of model output will be provided with model effects presented both as estimates with associated 95% CIs and also, where appropriate, as plots to visualise the time course of fitted outcomes.

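### The sample-size section says 220 patients reliably exclude sensitivity below 84% and specificity below 59%, but these are only expected lower confidence limits, and at the assumed values each is excluded only about half the time

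*Protocol article*

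**What the plan says.** The protocol article's Sample size section sizes the study on precision. Its stated aim is to "estimate a 95% CI for sensitivity (with a maximum width of 10%) and for specificity (with a maximum width of 20"%. The calculation was repeated over a span of sepsis prevalences, from 50% up to 70%. The section then fixes its assumptions. On prevalence it writes "Assuming a prevalence of sepsis of at least 60"%. Sensitivity is taken to be 90% or more, and specificity 70% or more. From these it concludes that "a total of 220 patients would allow us to reliably rule out a sensitivity less than 84% and a specificity of less than 59"%. Allowing for 10% drop-out, 220 becomes 245.

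No probability of achieving the exclusion is given, and the section names no interval method. The Data analysis section names one for a reported proportion, "95% CIs calculated by binomial exact methods", and asks simply for 95% CIs for sensitivity and specificity.

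**The concern.** Saying that a design reliably rules out a value is a claim about probability: if the assumptions hold, the lower confidence limit will usually lie above that value. A lower limit computed by setting the observed proportion equal to the assumed true one has no such property, because the observed proportion falls below the truth roughly half the time.

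Two other parts of the same sentences looked doubtful. The first is whether 132 septic patients deliver the stated maximum width for sensitivity. The second is whether a lower bound on prevalence can protect specificity, since higher prevalence leaves fewer non-septic patients.

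At stake is how readers understand the only quantitative justification given for 220 and 245 patients, in a study whose primary objective is to validate the biomarkers.

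**Working it through.** **Inputs (all from Sample size unless noted).** N = 220; prevalence 60%, so septic n = 0.60 × 220 = 132 and non-septic n = 220 − 132 = 88; sensitivity 0.90; specificity 0.70; two-sided 95% intervals. The exact (Clopper–Pearson) method is taken from Data analysis. Wilson and Wald were tried as alternatives because Sample size names no method.

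**Step 1. Reproduce the plan's figures.** The exact lower limit for x events in n is the 2.5% quantile of Beta(x, n − x + 1); the upper limit is the 97.5% quantile of Beta(x + 1, n − x).
- Sensitivity, x = 0.90 × 132 = 118.8: 83.6% to 94.5%.
- Specificity, x = 0.70 × 88 = 61.6: 59.3% to 79.3%.
- Drop-out: 220 / 0.9 = 244.4, rounded up to 245.

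So 84%, 59%, 220 and 245 all reproduce. The first two are the lower limits when the estimates land exactly on the assumed values.

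**Step 2. Chance of excluding these limits at the assumed values.** For each method, find the smallest count whose lower limit reaches the bound, then take the binomial tail probability at 0.90 or 0.70. The joint figure is the product, treating the two as independent.

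| Method | Sensitivity: count needed, chance | Specificity: count needed, chance | Both |
|---|---|---|---|
| Exact | ≥120/132, 0.43 | ≥62/88, 0.52 | 0.22 |
| Wilson | ≥120/132, 0.43 | ≥61/88, 0.61 | 0.26 |
| Exact, limit need only round to 84% / 59% | ≥119/132, 0.55 | ≥61/88, 0.61 | 0.33 |
| Wald | ≥118/132, 0.66 | ≥61/88, 0.61 | 0.40 |

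None reaches 0.80 for either measure.

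**Step 3. Dependence on the true values (exact, 60% prevalence).** The chance of excluding 84% is 0.74 at true sensitivity 92%, 0.87 at 93% and 0.985 at 95%. The chance of excluding 59% is 0.87 at true specificity 75%.

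**Step 4. Width for sensitivity at 60% prevalence.**
- Wald: 2 × 1.96 × √(0.9 × 0.1 / 132) = 10.2%.
- Wilson: 10.3%.
- Exact: 94.5% − 83.6%, or 11.0% before rounding of the limits.

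All exceed the stated 10% maximum. A 10% width needs 139 septic patients (Wald) or 158 (exact), against 132. The specificity width is 20.0% exact, 18.8% Wilson and 19.1% Wald, so that target is met or essentially met.

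**Step 5. Prevalence (exact limits, N = 220).**

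| Prevalence | Septic / non-septic | Sensitivity 95% CI (width) | Specificity 95% CI (width) |
|---|---|---|---|
| 50% | 110 / 110 | 82.8–94.9% (12.1%) | 60.5–78.4% (17.8%) |
| 60% | 132 / 88 | 83.6–94.5% (11.0%) | 59.3–79.3% (20.0%) |
| 65% | 143 / 77 | 83.9–94.4% (10.5%) | 58.5–79.9% (21.4%) |
| 70% | 154 / 66 | 84.1–94.2% (10.1%) | 57.5–80.7% (23.2%) |

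At 65% and 70% prevalence the specificity width exceeds 20% by exact, Wilson and Wald alike. The exact chance of excluding 59% falls from 0.52 at 60% to 0.45 at 65% and 0.37 at 70%.

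**Step 6. What 220 patients do exclude with about 80% probability.** With exact intervals at the assumed values, the lower limit for sensitivity is at or above 81% when at least 116/132 are detected (probability 0.83). For specificity it is at or above 55% when at least 58/88 are correctly negative (probability 0.83). Jointly, 0.83 × 0.83 = 0.69.

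**The case against.** The strongest reply is that this is ordinary precision-based sizing, that its arithmetic is correct, and that the only fault is one adverb. The first two parts stand. The third does not quite, because the width for sensitivity and the prevalence condition are also misstated.

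The low probabilities also need context. They apply at the bottom of the stated assumptions, and the shrinkage-adjusted estimates from the previous study were higher (sensitivity 1.00, specificity 0.75). Part of the 0.43 is rounding, since the plan's own limit is 83.6%. This tempers the size of the problem. It does not remove it, because the sentence makes its promise for values of at least 90% and 70% and must therefore hold at exactly those values.

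On prevalence, the loss is gradual. The exact lower limit for specificity still rounds to 59% up to about 64.5% prevalence, the previous study observed 61%, and by Wald the limit is 58.9% even at 70%. The width for sensitivity is missed by only 0.2 to 1.0 percentage points at 60% prevalence, and Wald and Wilson meet 10% at 65%.

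A reader might infer that a sound test would probably be declared a failed validation. The document does not support that. Data analysis sets no success threshold; it reports accuracy estimates with 95% CIs, and 84% and 59% appear only in the sizing argument.

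**Conclusion.** The concern holds as a misstatement of what the design delivers. At sensitivity 90%, specificity 70% and 60% prevalence, the stated limits are excluded with probability about 43–66% and 52–61%, and both together about 22–40% assuming independence. That is not reliable exclusion. The 10% maximum width is narrowly missed at 60% prevalence (10.2% to 11.0%). The condition of at least 60% prevalence protects sensitivity but not specificity: across 60% to 70% the exact lower limit falls from 59.3% to 57.5% and the width grows from 20.0% to 23.2%.

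These results rest on two-sided 95% intervals and on 220 evaluable patients. They improve if true performance exceeds the assumed minimum. No analysis or decision rule in the document depends on the sentence, so this is a worthwhile correction but not a critical one. It does not show that the study is too small for its stated purpose of estimating accuracy.

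**What to change.** In Sample size:

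1. Delete *reliably*, and describe 84% and 59% as the lower exact 95% limits expected at 60% prevalence if the observed sensitivity and specificity are 90% and 70%.
2. Name the interval method, and restate the expected width for sensitivity as about 11% (exact).
3. Replace the one-sided prevalence condition with expected limits and widths for both measures at 50%, 60% and 70% prevalence, as in the table above.
4. If an assurance statement is wanted, say that at 60% prevalence 220 patients exclude sensitivity below about 81% and specificity below about 55% with roughly 80% probability each, and give the joint probability (about 65–70%).

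The cost is wording only. No extra patients are needed, and the stated figures become slightly less favourable. Keeping 84% and 59% with 80% probability each would instead need about 460 evaluable patients for sensitivity and 400 for specificity at 60% prevalence (exact), which is not proposed here.
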